#### Imaging protocol

The initial clinical head CT data from the emergency room will be downloaded. Lesion characteristics will be documented in REDCap, including intracranial pathologies, subarachnoid hemorrhage, extra-axial or subdural hemorrhage, as well as findings related to cisterns and surgeries based on NIH Comment Data Elements. MRI scans will be collected at 3 months (±2 weeks) and 12 months (±1 month) post-injury, and analyses will account for the impact of lesion location and size on a subject-by-subject basis.

MRI data will be collected on a Siemens Prisma 3 T scanner: (1) 3D Multi-Echo T1-weighted Magnetization-Prepared-Rapid-Acquisition-of-Gradient-Echo (3D ME-MPRAGE) sequence (32) will be used to measure brain volumes. (2) 3D T2 FLAIR sequence (32) will be used to assess white matter hyperintensity volume and location (33). (3) 3D Multi-Echo Gradient Recalled Echo (3D ME-GRE) (32) will be used to visualize and quantify microbleeds and hemorrhage (34).

(4) 3D Pseudo Continuous Arterial Spin Labeling (3D PCASL) sequence will be used to measure regional CBF (35, 36). (5) Diffusion tensor imaging (DTI) with multiple b values, including 114 diffusion-weighted image volumes, will be used to assess white matter microstructural integrity (37). (6) Resting-state fMRI (rs-fMRI) will be used to assess brain network functional connectivity with a focus on the DMN (Default Mode Network) (38–42).

Each MRI scan will be visually reviewed within three business days. Preliminary processing will generate maps including FreeSurfer T1 segmentation, R2*, SWI, QSM, ASL perfusion, DTI FA/MD, fiber tracking, and resting-state fMRI SNR/connectivity. [name] (MRI physicist) or his trainee will assess image quality. Inferior image quality is often due to motion, acquisition errors, or system issues. Imaging sequences with inferior quality will be marked, and rescanning will be attempted if feasible. Poor-quality sequences will not be included in final analyses.

##### TBI lesion characterization

A neuroradiologist will visually review T1, T2 FLAIR, and GRE images (the R2*, SWI and QSM maps genrated from the multi-echo GRE images as well) to assess “lesion load.” Participants with large lesions (>5 cm^3^ subcortical, >50 cm^3^ cortical) will be excluded from automated analysis, but DTI metrics and CBF will be examined on these lesions. Case-by-case approaches will address large lesions.

##### Volumetric data processing

3D T1 MPRAGE images will undergo a series of FreeSurfer-based processing procedures to generate cortical and subcortical morphometrics (43, 44). To improve the cortical surface reconstruction, T2 FLAIR data will be incorporated into FreeSurfer’s reconstruction pipeline (45). To reduce the potential impact of brain lesions due to TBI on cortical surface reconstruction, we will visually inspect each segmentation and manually label and remove vertices on the cortical surfaces caused by the lesions (45). The scans which fail to complete the processing pipeline or require major manual edits will be excluded for further analysis (45). The corrected maps and regional volumes will be used for further post-processing.

#### rs-fMRI data processing

We include rs-fMRI as an exploratory measure of changes in brain neural network connectivity after TBI (40). AFNI (Analysis of Functional NeuroImages) will be used for rs-fMRI data preprocessing (55). A robust independent component analysis based preprocessing strategy will also be assessed (40). The DMN functional connectivity has been demonstrated to be an important marker in AD (41) and TBI (56). The nodes of the DMN network as well as other networks can be extracted with the atlas published by Yeo et al. (57) in young adults or by Shirer et al. in older adults (58). The overall DMN functional connectivity, and similarly for other networks, at each time point will be calculated as the average of the pair-wise Pearson correlation coefficients of all connection pairs of DMN nodes and will be used for within-subject as well as for group comparisons (40).

##### Image analysis integration

All MRI images will be aligned to the T1 MPRAGE images which will be standardized to the MNI305 space via the FreeSurfer processing pipeline (46). Primary analysis will be carried out in the subject space. Voxel-based group analysis will be carried out in the MNI space.

##### Arterial spin labeling (ASL) data processing

CBF maps will be generated from pCASL sequence based on the equation proposed by the ISMRM Perfusion Study Group (35, 47).

##### DTI data processing

The DTI data will be processed with FSL (48). The “topup” procedure will be used to correct susceptibility distortions (49). The Track-Based Spatial Statistics program (50) will be used to estimate fractional anisotropy, mean diffusivity, axial diffusivity, and radial diffusivity (51, 52). Free water content will be estimated with the DIPY software package (53). Probabilistic tractography will be performed to estimate brain network structural connectivity (40, 41, 54).

#### Functional and cognitive outcomes at 3, 6, and 12 months

A detailed neuropsychological assessment will be administered by research staff trained and supervised by a neuropsychologist at all three followup time points and will take approximately 2.5 to 3 h. The screening assessment, including the GOAT and speech intelligibility, will be evaluated either by phone or in person (Table 2).

#### Cognitive outcomes

This assessment will include primary outcome measures that tap into a variety of cognitive domains in person during the follow up visit, as reflected by various measures in the computerized National Institutes of Health (NIH) Toolbox. The NIH Toolbox Cognitive Battery, administered via iPad, includes 7 subtests to assess executive function, attention, episodic memory, working memory, processing speed, and language. We also will perform the Hopkins Verbal Learning Test (HVLT) to assess episodic memory, the Trail Making Test for attention, speed, and mental flexibility and Processing Speed Index (WAIS-IV PSI) and SWAPS (aka TAPS).

#### Functional outcomes

Secondary outcome measures will include the Glasgow Outcome Scale Extended-Revised (R-GOSE) (59), Functional Status Examination (FSE), Expanded Disability Rating Scale Post-Acute Interview (E-DRS-P), and Functional Independence Measure (FIM).

#### Psychological health and quality of life

Psychological health, sleep, stress, and quality of life will also be evaluated using various measures popular measures including the PROMIS PROPr Short form (PROMIS-29 Profile V2.1), Pittsburgh Sleep Quality Index (PSQI), and PTSD Checklist for Civilians (PCL-C), among others (Table 2).

Furthermore, for participants who are unable to take Comprehensive Assessment Battery the abbreviated Assessment Battery will be assessed within 1–15.5 h using the Confusion Assessment Protocol (CAP), Coma Recovery Scale-Revised (CRS-R), R-GOSE, FSE, Expanded Disability Rating Scale Post-Acute Interview (E-DRS-P), and FIM (Table 2).

#### Data management and quality assurance

A REDCap database will be developed to collect and store data (60). The REDCap database will be hosted on a secure, HIPAA compliant server at the University of Texas Southwestern Medical Center. The study coordinator will use REDCap’s data quality control module to report missing values, validation errors, and outliers, as well as run simple reports using REDCap. All MRI subject data will be collected without identifiable subject information and will be uploaded to a secured data server.

### Power and sample size

This study is powered to examine the relationship between the primary outcome of NIHTB_CB fluid composite score at 1-year postinjury and dynamic CA indices derived from frequency-domain analysis during the acute stage of TBI (i.e., <1-week postinjury). According to our previous study (13), the dynamic CA transfer function phase at low frequency range was positively correlated with NIHTB_CB fluid composite score (i.e., a higher phase, a better CA, was associated with better cognitive score), with the coefficient of determination (
$R^{2}$
) of 0.35 (or Pearson correlation coefficient = −0.593). Based on this information, it is estimated that 117 participants (i.e., a cohort of TBI *n* = 90 and orthopedic controls *n* = 27) will provide 82% power at a 5% two-sided significance level to detect a 0.053 increase in 
$R^{2}$
 attributed 2 additional dynamic CA variables (transfer function gain and coherence), adjusting for 6 confounding factors (initial GCS, posttraumatic amnesia, head CT scan, age, sex, and education) in a multiple regression model, where 
$R^{2}=$
0.35 when only the control factors are included in the model (NCSS PASS 16). With a 10% attrition rate, the total sample size of *n* = 130 participants (TBI = 100, control = 30) are required to be enrolled for this study.

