## Methods and analysis

### Aim of the study

Our primary research aim is to determine if acute cerebrovascular dysfunction after TBI is associated with cognitive outcome at 1-year post-injury. Secondly, to determine the temporal associations between the recovery of cerebrovascular function and cognitive outcomes after TBI. The third aim is to determine the temporal associations of acute cerebrovascular dysfunction and its recovery with imaging biomarkers of neurodegeneration after TBI.

We expect that the severity of cerebrovascular dysfunction during the acute stage will be inversely associated with cognitive outcomes and functional outcomes at 1-year post-injury. Additionally, we also anticipate that, compared to an orthopedic control (OTC) group with no TBI history, the TBI patients will exhibit impaired dynamic CA in the acute phase. Assessments of CA during the acute stage of TBI are expected to independently predict functional and cognitive outcomes at 1-year post-injury. The results of this study could pave the way for innovative vascular-focused interventions aimed at enhancing cognitive recovery and mitigating neurodegeneration following TBI (Figure 1).

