**Figure 1 fig1:**
[figure not shown]
The figure illustrates the participant timeline. TBI, traumatic brain injury; MRI, Magnetic Resonance Imaging. * MRI will be performed at 3 and 12 months. **6 months follow-up will be only done in TBI group.

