#### Study population

Patients aged between 18 and 80 years old, within 1-week post-injury, and admitted to the hospital for moderate to severe TBI and/or mild TBI with neuroimaging abnormalities are eligible for inclusion (see Table 1). Additionally, individuals with orthopedic injury without TBI can participate as a control group if they meet the inclusion criteria outlined in Table 1 and do not meet any of the exclusion criteria.

**Table 1 tab1:** Eligibility criteria.

Inclusion Criteria for TBI Group A documented moderate to severe TBI posttraumatic Amnesia (PTA) > 24 h Loss of consciousness (LOC) >30 min Global cognitive score (GCS) <13, or Intracranial neuroimaging abnormalities (Head CT or MRI) Mild TBI with abnormalities on imaging exam. Ages 18–80 years-old 1 week post injury and admitted to the hospital for TBI. All participants must be fluent in English or Spanish. Inclusion Criteria for non-TBI Orthopedic Control Group: Abbreviated Injury Score of ≤4 (not life threatening) for extremity and/or pelvis injury and/or rib fracture Without evidence of TBI based on history or head CT 1 week post injury and admitted to the hospital for trauma. All participants must be fluent in English or Spanish. Exclusion Criteria for the study Significant polytrauma that would interfere with follow-up and outcome assessment. Major debilitating baseline mental health disorders, major debilitating neurological disease, impairing baseline awareness, cognition, or validity of follow-up and outcome assessment. Significant history of pre-existing conditions that would interfere with follow-up and outcome assessment (e.g., end-stage cancers). Patients on psychiatric hold. Prisoners or patients in custody, pregnancy, low likelihood of follow-up (e.g., participants or family indicating low interest, residence in another state or country, homelessness or lack of reliable contacts). Current participant in an interventional trial (e.g., drug, device, behavioral). Penetrating TBI, spinal cord injury with ASIA score of C or worse and contraindications to MRI.

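### The stated 82% power counts 27 controls without TBI; in the 90 evaluable TBI patients, to whom the primary aim refers, the same test has about 70% power

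*Protocol article*

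**What the plan says.** Aim of the study sets the primary question within TBI: "Our primary research aim is to determine if acute cerebrovascular dysfunction after TBI is associated with cognitive outcome at 1-year post-injury". Power and sample size likewise describes the powered relationship as one between the 1-year NIH Toolbox fluid composite and CA indices from the acute stage of TBI.

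The same section then takes its sample from both cohorts. The sentence opens "Based on this information, it is estimated that 117 participants (i.e., a cohort of TBI" and itemises 90 TBI patients plus 27 orthopedic controls. This number "will provide 82% power at a 5% two-sided significance level to detect a 0.053 increase in" R² from adding two CA measures, the gain and the coherence of the transfer function. The adjustment is worded as "adjusting for 6 confounding factors (initial GCS, posttraumatic amnesia, head CT scan, age, sex, and education) in a multiple regression model". The R² for those factors alone is put at 0.35. Allowing 10% attrition, 130 are to be enrolled: 100 TBI and 30 controls.

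Table 1 admits controls only "Without evidence of TBI based on history or head CT". The opening section of the Statistical analysis plan uses controls for a two-sample comparison of acute CA. Statistical methods: outcomes gives the primary linear regression and its confounders and adds automatic forward, backward and stepwise selection. It names neither the cohort in which the model is fitted nor a TBI/control term.

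**The concern.** Power belongs to a particular test in a particular set of people. Here the set includes 27 people who cannot have cerebrovascular dysfunction after TBI, while the question is whether such dysfunction goes with later cognition. The two readings of the plan lead to different faults:

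- **The primary regression is fitted in TBI patients only.** The effective sample is 90, not 117, and the stated power is too high.
- **The primary regression is pooled.** The sample size is right, but the CA coefficient is no longer clearly the association within TBI. The plan itself expects TBI patients to have worse acute CA than controls. If their cognition is also lower, part of a pooled coefficient can come from the difference between groups.

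At stake is either the chance of detecting the planned effect or the meaning of the primary coefficient.

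**Working it through.** **Inputs, all from Power and sample size.** R² increment ΔR² = 0.053; R² of the control factors R²c = 0.35; 2 tested variables; 6 covariates; α = 0.05; N = 117 = 90 + 27; attrition 10%.

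**Formulas (partial F test, fixed regressors).**
- f² = ΔR² / (1 − R²c − ΔR²) = 0.053 / 0.597 = 0.0888
- noncentrality λ = N·f²; degrees of freedom 2 and N − 9
- power = P(noncentral F > 95th percentile of central F)

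**Step 1: reproduce the plan's figure.** N = 117: λ = 10.39, df = (2, 108), power 81.95%, which is the stated 82%. The attrition step also holds: 117/0.9 = 130, 90/0.9 = 100, 27/0.9 = 30.

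**Step 2: change only N.**

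| Sample | λ | df | Power |
|---|---|---|---|
| 117 (TBI + controls) | 10.39 | 2, 108 | 81.95% |
| 100 (all enrolled TBI, no attrition) | 8.88 | 2, 91 | 75.0% |
| 90 (evaluable TBI) | 7.99 | 2, 81 | 69.98% |

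Other conventions give a similar drop. With λ taken as error df × f², power is 78.6% at 117 and 65.1% at 90. With random regressors (simulation, 20,000 runs), it is 78.7% and 65.4%.

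**Step 3: what 90 TBI patients can detect.** With the other inputs fixed, 80% power needs ΔR² of about 0.0655 and 82% power about 0.068. To keep ΔR² = 0.053 at 80% power would take 112 evaluable TBI patients, or 112/0.9 = 124.4, rounded up to 125 enrolled.

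**Step 4: sensitivity.** The document gives no R² values for TBI alone, so steps 2 and 3 carry over the plan's own. At N = 90 and ΔR² = 0.053, power is 63% for R²c = 0.25, 70% for 0.35 and 78% for 0.45. At R²c = 0.35, ΔR² = 0.06 gives 76%.

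**Step 5: what a pooled coefficient estimates.** The documents give no slopes by group, so this is an illustration on assumed values: within-group SD 1 for CA and cognition, TBI lower by 0.8 SD on both, slope 0.25 in TBI and 0 in controls, no other covariates. The cohort shares are 90/117 = 0.769 and 27/117 = 0.231, with product 0.1775.
- No group term: (0.769 × 0.25 + 0.1775 × 0.8 × 0.8) / (1 + 0.1775 × 0.8²) = (0.1923 + 0.1136) / 1.1136 = 0.27, above the TBI slope.
- Group indicator but a common slope: (90 × 0.25 + 27 × 0) / 117 = 0.19, below it.
- Group indicator and a true slope of 0.25 in both groups: 0.25, no distortion.

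The direction therefore depends on the adjustment and on the control slope, and the plan fixes neither.

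**The case against.** The strongest reply is that the calculation is correct and a pooled regression is legitimate. Controls have acute monitoring and 12-month cognitive testing. They can be coded on the injury covariates as normal GCS, no amnesia and no TBI on head CT, and that coding adjusts partly for group. They inform the age, sex and education coefficients and the residual variance, and the CA slope too if it is the same in both groups. An article may also leave the analysis population to the full protocol or SAP.

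Much of this stands, and it rules out some stronger readings:

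- A reader might infer that controls add no information. That holds only if nothing is shared between the groups, which the documents do not say.
- A reader might infer that the injury covariates exist only in TBI. They can be coded in controls, and because mild TBI with abnormal imaging is eligible, GCS values can overlap between cohorts.
- A reader might infer that pooling biases the slope by a known amount. Step 5 shows that it can move either way or not at all.
- A reader might infer that lost power and a mixed coefficient both apply. They are alternatives, depending on which model is meant.

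The appeal to an unseen SAP does not settle the matter. This article expressly counts controls toward power for a question it places within TBI. Nor are the injury covariates a secure substitute for a group term: they are partial proxies, and automatic selection may drop them. The plan does not state that the slope is assumed equal in the two groups.

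**Conclusion.** The point holds. For the stated question, in the 90 evaluable TBI patients, power is about 70% against a stated 82%, a shortfall of about 12 points (about 13 under the other two conventions). The error lies in who is counted, not in the arithmetic.

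The 70% rests on ΔR² = 0.053 and covariate R² = 0.35 applying unchanged within TBI. If a pooled model is intended, 82% is correct for that model, and the fault is that its CA coefficient does not isolate the association within TBI. The documents do not allow that distortion to be sized. Under either reading, the power statement and the primary aim need to be reconciled before analysis.

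**What to change.** - In Statistical methods: outcomes, state that the primary regression is fitted in the TBI cohort.
- In Power and sample size, restate the power for 90 evaluable TBI patients: about 70% for ΔR² = 0.053 on 2 df, or 82% for ΔR² of about 0.068, with the assumption about R² made explicit. If a 1-df test of one CA index is quoted instead (79.8%, about 80%), say that it assumes this single index carries the whole 0.053, which is a different hypothesis from the two-variable increment.
- Keep the controls for the TBI-versus-control comparison of acute CA.
- Make any pooled regression secondary, with a group indicator and a group-by-CA interaction that are not subject to automatic selection.

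The cost is wording in two sections and a less favourable stated power. No extra patients are needed unless the sponsor wants to restore 80% power for ΔR² = 0.053, which would mean about 125 TBI enrolled instead of 100.

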### Statistical analysis plan

Discrete variables will be summarized using counts with percentages, and continuous variables using means with standard deviation or medians with interquartile ranges. The comparisons between TBI and OTC groups in dynamic CA indices during the acute phase will be evaluated using a two-sample t-test or nonparametric Wilcoxon test. No adjustment will be made for multiple comparisons, and therefore findings for secondary outcomes should be interpreted as exploratory. Two-sided 0.05 level of significance will be used for statistical hypothesis testing.

#### Statistical methods: outcomes

For the primary analysis, multiple linear regression models will be performed to examine the associations of dynamic CA indices on the primary outcome of NIHTB_CB fluid composite score at 1 year post injury, adjusted by potential confounders (i.e., initial GCS, posttraumatic amnesia, head CT scan, age, sex, etc.). The parsimonious model will be selected via the automatic model selection algorithms, including forward, backward, and stepwise selection. Multicollinearity will be evaluated using variance inflation factors, and the issue of overfitting will be assessed through 10-fold cross-validation. For the secondary analyses, secondary outcomes, including CA/CBF and other continuous cognitive measures, R-GOSE score as well as health-related PROMIS measures at 1-year postinjury, will be analyzed separately through the same analytical approach. Sensitivity analyses of the outcomes will be performed to assess the robustness of the findings, including model diagnostics, outlier assessments, distributional assumptions, and missing data. Data transformation will be made if the normality assumption is violated.

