### Follow-up retention plan

The participant or the LAR will be approached at 3 months (±2 weeks), 6 months (±2 weeks), and 12 months (±1 month) for follow-up assessments (Figure 1). For follow-up, participants will be invited to come on 2 days’ visits. On the first day, the patient will undergo a physical neurological exam, as well as cognitive and functional assessments (Table 2). On the second day, a cerebral vascular assessment will be conducted. The MRI will be performed at the University of Texas Medical Center during the first day visit at 3 and 12 months (Figure 1). If participants are still hospitalized at these time points, the follow-up will take place there.

**Table 2 tab2:** Functional, cognitive and psychological health and quality of life.

Domain	Outcome measures	Time points	Interview type
Screening assessment			
	Speech intelligibility	3 M, 6 M*, 12 M	T, IP
	GOAT	3 M, 6 M*, 12 M	T, IP
Comprehensive assessment battery			
Cognition (primary outcome)	NIHTB cognitive battery	3 M, 6 M*, 12 M	IP
	Hopkins Verbal Learning Test (HVLT)	3 M, 6 M*, 12 M	IP
	Trail Making Test	3 M, 6 M*, 12 M	IP
	Processing Speed Index (WAIS-IV PSI)	3 M, 6 M*, 12 M	IP
	SWAPS (aka TAPS)	3 M, 6 M*, 12 M	IP
Global outcomes (secondary outcome measures)	Functional Status Examination (FSE)	3 M, 6 M*, 12 M	T, IP
	Revised Glasgow Outcome Scale Extended (R-GOSE)	3 M, 6 M*, 12 M	T, IP
	Expanded Disability Rating Scale Post-Acute Interview (E-DRS-P)	3 M, 6 M*, 12 M	T, IP
Psychological health and quality of life (secondary outcome measures)	PROMIS PROPr Short form (PROMIS-29 profile V2.1)	3 M, 6 M*, 12 M	T, IP, R
	Pittsburgh Sleep Quality Index (PSQI)	3 M, 6 M*, 12 M	T, IP, R
	NINDS Epilepsy Screening Questionnaire	3 M, 6 M*, 12 M	T, IP
	Rivermead Post-Concussion Questionnaire (RPQ)	3 M, 6 M*, 12 M	T, IP, R
	Patient health Questionnaire-9 (PHQ-9)	3 M, 6 M*, 12 M	T, IP, R
	Columbia Suicide Severity Rating Scale (C-SSRS) (only required if >1 on thePHQ-9 #9)	3 M, 6 M*, 12 M	T, IP
Abbreviated assessment battery for participants who are unable to take comprehensive assessment battery			
Consciousness and basic cognition	Confusion Assessment Protocol (CAP)	3 M, 6 M*, 12 M	IP
	Coma Recovery Scale Revised (CRS-R)	3 M, 6 M*, 12 M	IP
Global outcome	Functional Status Examination (FSE)	3 M, 6 M*, 12 M	T
	Revised Glasgow Outcome Scale Extended (R-GOSE)	3 M, 6 M*, 12 M	T, IP
	Expanded Disability Rating Scale Post-Acute Interview (E-DRS-P)	3 M, 6 M*, 12 M	T, IP

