#### Physiological data processing

Cerebrovascular and cardiovascular data will be analyzed using AcqKnowledge (BIOPAC Systems, Goleta, CA), DADiSP (DSP Development Corporation, Newton, MA), MATLAB (MathWorks, Natick, MA) and ICM+ software (22, 23).

Dynamic CA assessed through the different monitoring modalities will be determined in two ways: time domain and frequency domain analyses. Time domain indices are based on the relationship between spontaneous changes in mean arterial pressure (MAP) and CBFV (10, 24–26).

Frequency domain analysis based on MAP-CBFV (TCD-derived), and MAP-Oxyhemoglobin (NIRS-derived) transfer functions will be computed bilaterally in each participant following an international Cerebrovascular Research Network (CARNet) guideline (22). Signals will be sampled (500 Hz) and stored for offline analysis. All signals will be filtered with an eighth-order Butterworth low-pass filter with a cut-off frequency of 20 Hz. The beginning and end of each cardiac cycle will be detected in the BP signal, and mean BP, CBFV and heart rate will be obtained for each heartbeat. Beat-to-beat parameters will be interpolated with a third-order polynomial and resampled at 5 Hz to generate signals with a uniform time base (22). Different TFA parameters (gain, phase, coherence) – will be calculated at very low frequency (VLF, 0.02–0.07 Hz), low frequency (LF, 0.07–0.2 Hz), and high frequency (HF, 0.2–0.5 Hz) ranges (27). Transfer function gain quantifies the magnitude relationship between input and output signals (such as systolic BP and MAP). The phase measures the temporal displacement between the input and output signals, and the coherence measures the strength of the linear relationship between the input and output signals (28).

A final averaged value from the bilateral TCD and NIRS measurements for each index will be calculated to assess *CA.* The CA of affected and unaffected hemisphere side by cranial CT scan will be also analyzed. We propose to use the transfer function phase as the primary measure of CA for its sensitivity and reliability to detect cerebrovascular dysfunction as demonstrated by our team and others (13).

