#### Statistical analysis: additional analyses

Mixed-effects models with an unstructured covariance matrix will be used to estimate the primary outcome of brain volumes measured at 3 and 12 months postinjury; the models will include subjects as random effect and dynamic CA indices, time, and dynamic CA indices 
×
 time interaction as fixed-effects factors. Other covariates or potential confounders (e.g., age, sex, dynamic CA indices and others) will be included in these mixed-effects models. Conditional Akaike information criteria and other goodness of fit criteria will be applied to select the parsimonious mixed-effects model. Similar modeling and data analysis will be applied with DTI measure of white matter integrity as a dependent variable. In the secondary analysis, mediation models will be performed to study the overall association of Δ CA and CBF variables (both global CBF measured by 2D color-coded duplex ultrasonography and regional CBF measured by ASL) with the outcome of Δ NIHTB_CB fluid composite score and to estimate the extent to which this association is mediated by Δ brain volumes or white matter integrity. We will repeat the above procedures for the DMN connectivity from rs-fMRI to explore if the associations between cerebrovascular function recovery, cognitive and functional outcomes are mediated by changes in brain neural network connectivity. Secondary outcomes, including changes in cognitive outcomes, R-GOSE score and PROMIS measures, will be analyzed followed by similar analytical approaches, and evaluated both total effects of Δ CA/CBF variables and mediation effects of Δ brain volumes. No adjustments for multiple comparisons will be made for all secondary analyses, which are considered as exploratory analyses. Assumptions and diagnosis for mixed-effects models will be carefully evaluated. Missing data will be imputed using multiple imputation by chained equations and pattern mixture approaches as needed and evaluated by the sensitivity analyses.

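### The primary exposure test is stated in three ways that do not agree: phase is named primary, gain and coherence are powered, and unlisted indices are analysed under automatic selection

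*Protocol article*

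**What the plan says.** All references are to the protocol article.

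- *Physiological data processing* derives gain, phase and coherence in three frequency bands, from both transcranial Doppler (TCD) and near-infrared spectroscopy (NIRS). It proposes phase as the primary autoregulation measure and attaches no band to that choice. It also states: "A final averaged value from the bilateral TCD and NIRS measurements for each index will be calculated to assess" autoregulation.
- *Power and sample size* concerns "the primary outcome of NIHTB_CB fluid composite score at 1-year postinjury and dynamic CA indices derived from frequency-domain analysis". It cites an earlier correlation between low-frequency phase and the fluid composite. The increment that it powers is for two other variables, gain and coherence, over six confounders.
- *Statistical methods: outcomes* states, as its primary analysis, that "multiple linear regression models will be performed to examine the associations of dynamic CA indices on the primary outcome of NIHTB_CB fluid composite score". Covariates are named with an open-ended list. It continues: "The parsimonious model will be selected via the automatic model selection algorithms, including forward, backward, and stepwise selection". Phase is not mentioned again.
- *Statistical analysis plan* states: "No adjustment will be made for multiple comparisons, and therefore findings for secondary outcomes should be interpreted as exploratory". *Statistical analysis: additional analyses* and the *Discussion* also confine the waiver to secondary outcomes and analyses.
- Outcome labels vary. The power and primary analysis sections both use the fluid composite at 1 year. Table 2 heads a row of five cognitive instruments "Cognition (primary outcome", *Cognitive outcomes* says "This assessment will include primary outcome measures that tap into a variety of cognitive domains", and the mixed models "will be used to estimate the primary outcome of brain volumes measured at 3 and 12 months postinjury".

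**The concern.** A primary analysis with a stated power and a two-sided 5% level needs one identifiable test. Here three sections point to three exposures: phase with no band, gain plus coherence jointly, and an open set of indices from which software picks. An analyst who followed the text could fit several models, or keep whichever index survived selection, and report the result as primary at 0.05. The exploratory caveat would not cover it, because that caveat is limited to secondary findings.

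Two things are at stake. The false-positive rate of the primary finding is not controlled, and the power statement does not describe the test that will be reported. This goes beyond detail that an article leaves to a fuller plan: the statements are in the article, and they disagree.

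**Working it through.** **1. Reproduce the stated power.** Inputs from *Power and sample size*: N = 117, 6 control variables with R² = 0.35, 2 tested variables (gain, coherence), R² increment 0.053, two-sided 5%.

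- f² = 0.053 / (1 − 0.35 − 0.053) = 0.053 / 0.597 = 0.0888
- noncentrality = 117 × 0.0888 ≈ 10.4
- df = 2 and 117 − 2 − 6 − 1 = 108
- power from the noncentral F distribution = 0.8195, against the stated 82%
- enrolment = 117 / 0.90 = 130, as stated

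The arithmetic is right, but only for one joint 2-df F test of gain and coherence in a fixed six-covariate model. If phase were an unlisted seventh control, power would be 0.8194, so the figure cannot show whether phase was meant to be in the base model.

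**2. False-positive rate if indices are tested one at a time at 0.05.** The article does not fix how many would be tested or how correlated they are, so both are assumptions. Three indices means phase, gain and coherence in one band; nine means 3 parameters × 3 bands. For independent tests the rate is 1 − 0.95^k. The simulation had no true index effect, N = 117, six covariates with R² = 0.35, and 4,000 runs.

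| Indices | Formula, independent | Simulated, correlation 0 | Simulated, correlation 0.5 |
|---|---|---|---|
| 3 | 1 − 0.95³ = 14.3% | 13.9% | 13.4% |
| 9 | 1 − 0.95⁹ = 37.0% | 37.1% | 27.5% |

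In the same runs a single joint F test of the whole set rejected in 4.3% to 5.4%, that is, near the nominal 5%. None of these figures includes stepwise selection. Its effect was not quantified, but a p-value read from a model chosen with the same data no longer has its nominal meaning.

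**3. Power of a single named test.** N = 117 and the same formula, assuming an increment of 0.053 whichever terms are tested:

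| Primary test | df | Power |
|---|---|---|
| One phase term | 1, 109 | 89% |
| Gain + coherence | 2, 108 | 82% |
| Phase + gain + coherence | 3, 107 | 76% |

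**4. Alternative: keep several primary tests.** With Bonferroni over an assumed three co-primary tests, the 2-df power falls to 68%. Restoring 82% needs 152 analysed, or 152 / 0.90 = 168.9, so 169 enrolled.

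**The case against.** The strongest defence has four parts.

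- **The outcome is settled.** The power and primary analysis sections agree on the fluid composite at 1 year, and the latter already places other continuous cognitive measures among the secondary outcomes. Brain volumes appear under additional analyses and match the third aim. This stands. A reader might infer six rival primary outcomes (five tests plus brain volume) and a 26% error rate from 1 − 0.95⁶. The text does not support that; what remains is loose labelling.
- **The index count is limited.** A reader might count 3 × 3 × 2 = 18 transfer function indices plus six time-domain indices, 24 in all, and quote 1 − 0.95²⁴ = 71%. That does not fit either, because the powered relationship is confined to frequency-domain indices. Nothing says that each of the 24 is a primary test.
- **Testing may be joint.** The power section describes an R² increment, and the collinearity check implies several indices in one model. This stands in part: a joint test of a fixed set would hold 5%. But the analysis section specifies neither the set nor the joint test, and it adds automatic selection.
- **The averaging sentence is probably harmless.** It can be read as pooling TCD with NIRS, which have different output signals. Left-right averaging within each modality is at least as natural, since the functions are computed bilaterally and the next sentence compares hemispheres. Pooling is one reading of an ambiguous sentence, not an established fault.

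The article never calls the test confirmatory, and its *Discussion* refers to an exploratory study. Even so, it defines a primary analysis with a level and a power, and its caveat on error rates reaches only secondary results. How daily sessions are summarised may properly sit in a fuller document.

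**Conclusion.** The point holds for the exposure. The article names phase as primary without a band, powers gain and coherence, and analyses an unlisted set of indices under automatic selection, with no multiplicity control for that primary analysis. The stated 82% is computed correctly but belongs to a test that the analysis section does not specify.

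The size depends on how the plan is carried out. The inflation to about 13–14% (three indices) or 27–37% (nine) applies only if indices are tested separately at 0.05, and it rests on assumed numbers and correlations. A prespecified joint test would show no such inflation. The outcome labels and the averaging sentence need tidying but do not enlarge the error rate. This should be corrected before outcome data are analysed.

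**What to change.** 1. In *Statistical methods: outcomes*, name one primary test against the 12-month fluid composite. One option is the TCD pressure-to-velocity phase at low frequency, averaged left-right and over acute sessions by one fixed rule. The other is one joint F test of a fixed, listed set.
2. Fit it in a model with prespecified covariates, for example the six in the power section, and exempt the tested term or terms from automatic selection.
3. State that all other indices are exploratory. If more than one primary test is kept, say how the 5% is shared.
4. Restate *Power and sample size* for the chosen test, using the figures in step 3 of the working and justifying the 0.053 increment for those terms.
5. Clarify in *Physiological data processing* that averaging is left-right within each modality, if that is the intention.
6. Align the labels: in Table 2 and *Cognitive outcomes* only the fluid composite is primary, and in the mixed-model paragraph brain volumes are the main outcome of the third aim.

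The cost is wording and one recalculated power statement. With a single primary test of one or two terms, the planned 130 participants suffice under the assumed increment; the three-term test would have 76%. Some indices lose any claim to primary status.
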